#### 2.5.2. Control Group (Usual Care)

Usual care includes individual counseling on the benefits of maintaining BF during the first 6 months and on the introduction of supplementary foods. The mother should be seen at least 6 times by the midwife and primary care pediatrician before the infant is 6 months old.

#### 2.5.3. Intervention Group (Mobile Application Group)

From the first recording during the first trimester, the women will be able to consult all the available information in the application. LactApp^®^ is a free access mobile application developed through Apple Store and Google Play, and can be consulted in English and Spanish [38,39]. The central function of LactApp^®^ is its automated nursing consultation structure. This tool also uses artificial intelligence and is available 24 h a day with a connection to the Internet, providing convenient and personalized support. LactApp^®^ includes a self-management form based on over 50 decision trees with questions and answers developed by nursing experts, and is supported by scientific evidence and current official health recommendations. The questionnaire generates over 2300 personalized replies that can be reached through over 76,100 potential routes that vary fitting to the profile of the users and the options selected by the latter. In addition, the application reminds the user about the following issues, depending on the entered date of birth:The first four weeks: positioning of the infant for breastfeeding, frequency of milk intake, number and consistency of stools, general care of the breast, and weight gain of the newborn. For women providing food supplements, the tool offers counseling and support for returning to breastfeeding.From months two to three: recommendations on milk extraction to create a reserve in case of having to return to work or leave home, with instructions on handling and storage of the collected milk.From months four to six: how to use the milk reserve (if any) and techniques for administering the stored milk, placing emphasis on the importance of supporting BF and the advisability of not using other types of feeding.

If the intervention is effective and differences are found between the two groups, an analysis will be conducted within the intervention group to analyze the profile of women who are less likely to abandon BF at 6 months based on baseline variables, by adjusting a multiple logistic regression model, estimating the corresponding ORs and 95%CIs.

### 2.6. Data Collection and Follow-Up

The collected data will be entered into an electronic form, guaranteeing confidentiality and anonymity, and ensuring compliance with the applicable regulations. Likewise, losses and dropouts during the trial will be detailed, along with the corresponding causes. In addition, e-mails will be sent to the mothers, inviting them to follow-up on breastfeeding using the self-administered questionnaire found on the created web platform.

The principal investigators will have access to the body of filtered data on the website created for the project, protected by a password, to be able to retrospectively enter the birth data and the number of postpartum visits to the different health professionals. In order to guarantee confidentiality, the data supplied to the project team members will not contain information capable of identifying the participants.

### 2.7. Baseline Variables

The following variables will be collected at baseline:

- Sociodemographic variables: maternal age at the probable date of delivery, country of origin (Spain/foreign), level of education (primary school or lower/secondary school/university), employment status (self-employment/professional/managerial employment/employee/unemployed/student/not looking for a job), civil status (single/married/separated-divorced), partner (yes/no), number of live offspring, previous experience with breastfeeding (yes/no), participation in maternal education groups (yes/no), reception of previous information on BF (yes/no), and participation in BF support groups (yes/no).

- Variables related to health literacy: as a screening tool, use will be made of the HLS-EU-Q16, which evaluates the HL of the population based on 16 items scored by means of a Likert scale from “very easy” to “very difficult”. This is a unifactorial scale with good internal consistency as measured by McDonald’s omega, with a value of 0.982 in the Spanish population [34].

- Variables referred to health-related quality of life: use will be made of the EQ-5D [40] in the baseline measurements and at 3 and 6 months. This scale is very sensitive to quality of life measures and has been shown to be even more sensitive in women [41]. It comprises 5 items related to mobility, personal care, daily activities, pain/discomfort, and anxiety/depression. It uses a visual analogue scale (VAS) from 0 to 100 for measuring health condition at the time of application of the questionnaire [42].

- Variables related to self-efficacy of BF: the measurement of self-efficacy will be made with the BSES-SF scale in its Spanish version [37]. This instrument consists of 14 items scored by means of a Likert scale from 1 (not at all) to 5 (always). The BSES-SF is a unidimensional scale with a Cronbach alpha of 0.79 in its Spanish version.

- Obstetric-neonatal variables. The following information will be collected retrospectively from the electronic case history: gestational age (days) at the time of birth, parity (none/one or more), type of previous deliveries (none/eutocic/other), onset of labor (spontaneous/induced/stimulated), rupture (spontaneous/artificial), group B streptococcus (positive/negative), intrapartum antibiotic use (yes/no), intrapartum analgesia (inhalatory/local/epidural/none), Kristeller maneuver (yes/no), completion of delivery (eutocic vaginal/eutocic instrumental (vacuum, spatulas, forceps), intrapartum cesarean section), episiotomy (yes/no), perineal condition following birth (intact/grade 1/grade 2/grade 3/grade 4), newborn gender (female/male), newborn weight (grams), Apgar score, umbilical arterial pH at birth, early skin-to-skin contact (within 30 min and lasting for at least 2 continuous hours) (yes/no/with father), early start of breastfeeding (within 2 h/after more than 2 h), drinking allowed during delivery (yes/no), accompaniment of maternal choice allowed (yes/no), mobilization allowed during delivery (yes/no), and positioning in moment of birth (vertical/lying down—lithotomy position/lateral decubitus).

- Response variable: type of nursing (BF/SF/MF) at 6 months postpartum, to assess newborn and infant feeding practices, with the following options: (a) BF, including extracted or donor milk. The infant only receives drops or syrups (vitamins, mineral, medicines); (b) SF (supplementary feeding), where infant feeding is limited to artificial formulas and solid; and (c) MF (mixed feeding), where infant feeding combines BF and SF. All women intend to offer BF after birth. The response variable “Suspension of BF at 6 months” (yes/no) will be considered, where “yes” means the infant is receiving SF and “no” means the infant continues with BF or MF at 6 months.

- Variables related to suspension of BF: type of suspension (total or partial), cause of early suspension (before 6 months postpartum), and total duration of BF in full days from time of birth.

- Follow-up variables: participation in support groups, and number of midwife/pediatrician/pediatric nurse visits during the first 6 months. Even if women suspend BF, the number of visits to these health professionals will continue to be counted for up to 6 months.

- Variables related to BF education received for 6 months: information/training in BF (none/previous information received from relatives, friends or health professionals (midwife, pediatric nurse, obstetrician, pediatrician)), consultation of texts, participation in birth preparation groups, nursing groups or postpartum groups, and the use of digital tools (yes/no/specify which).

- LactApp^®^ use will be assessed from women’s reports on the acceptability and convenience of the mobile application while during use. Data will be collected on the number of connections made, time of use, and topics consulted. All of these data will be provided by the company in an anonymized form. No private information resulting from the mobile application will be collected.

### 2.8. Data Analysis

An analysis will be performed of the baseline characteristics between the group of possible losses to follow-up and the group of women that complete follow-up, based on two-input tables and the comparison of means, using the Fisher exact test or Mann–Whitney U-test, as applicable.

Testing of the homogeneity of groups will be completed regarding the baseline variables and birth-related parameters and the suspension of BF at 6 months, using two-input tables and the chi-square test (χ^2^) or Fisher exact test, as applicable, while the comparison of means will be performed using the Mann–Whitney U-test.

A per-protocol (PP) analysis and intention-to-treat (ITT) analysis will be carried out. In the PP analysis, continuous variables will be reported as the mean and standard deviation (SD), or as the median and interquartile range (IQR) in the case of a non-normal data distribution, while categorical variables will be reported as frequencies and percentages. Data normality will be assessed using the Kolmogorov–Smirnov test.

In the ITT analysis, sensitivity referring to losses during follow-up will be assessed, with the response variable of the intervention group being assigned the worst result possible (suspension of BF at 6 months) and the control group being assigned the best result possible (no suspension of BF). Evaluation of the differences in response variable between the two groups will be performed, with all randomized subjects, applying the chi-square test.

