### 2.4. Sample Size Determination

Based on previous studies [15], and assuming the BF suspension rate at 6 months to be 60% in the control group versus 40% in the intervention group, with a significance level of *p* < 0.05 and a statistical power of 85%, a balanced design would require 333 women in total. Compensating for an estimated loss rate of 20%, the estimated final total sample size would be 399 women.

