## 4. Limitations

The present study has its limitations. The level of adherence or decisions of the pregnant women when the issue of breastfeeding is raised during the monitoring of pregnancy may depend on a number of factors such as the type of information given to the women and the way in which the health professionals communicate with them. In effect, we consider that favorable health outcomes to be largely dependent upon the complex interaction between the health professional and the patient or user. However, the aim of our study is to explore the patient-related factors that facilitate or complicate BF, such as poor health literacy, with reference to the body of literature cited in the protocol. Since there is currently no standardized and protocolized mechanism for determining the skills of pregnant women in making effective use of the information provided, we consider it prudent to assume that the information supplied will be more or less the same for each woman (LactApp^®^ + professional), and that women with limited HL will be more prone to making suboptimal decisions as a result. In view of these shortcomings, we feel that it will be difficult to find compensation mechanisms for these women. Logically, this does not obviate the individual efforts which the professionals may make to solve problems such as poor understanding or language issues. Nonetheless, we believe that the added complexity of trying to systematize and define such efforts falls beyond the scope of our study. Furthermore, a contamination effect could occur among the women participating in the study, relating to the exchange of information regarding the use of the mobile application. This could be detected through the periodic electronic nursing follow-up surveys, evaluating whether the women in the control group make use of online tools. Such use would be reason for exclusion from this study. Another limitation may be the number of losses over follow-up. The self-completed electronic survey via the Internet has many advantages such as speed of data collection, lower cost, and can provide an attractive design for the respondent [41]. The downside is that there may be a lower response rate, which may affect the results obtained. In order to control for such selection bias and break of randomization, an analysis will be performed of the characteristics of the group of dropouts, along with an intention-to-treat analysis.

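### The ITT comparison is described only through a one-directional worst-case rule, which at the plan's own loss rate erases or slightly reverses the planned benefit

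*Protocol article*

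**What the plan says.** Section 2.8 of the protocol article announces a per-protocol and an ITT analysis. The ITT paragraph opens by saying that sensitivity to losses will be assessed and then gives the rule for lost app women: "with the response variable of the intervention group being assigned the worst result possible (suspension of BF at 6 months"). Women lost from the other arm are coded in the opposite direction, so that the sentence ends with "the control group being assigned the best result possible (no suspension of BF"). The arms are then compared by chi-square with every randomized woman included. No other treatment of missing 6-month status is given.

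Section 2.8.1 (primary outcome) specifies a chi-square test and a logistic regression but names no analysis set. Section 2.7 makes suspension the unfavourable outcome; exclusive and mixed breastfeeding both count as not suspended.

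Section 4 raises the risk of a low response rate and brings in the ITT analysis, alongside a description of dropouts, for this purpose: "In order to control for such selection bias and break of randomization".

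Section 2.4 supplies the planning figures. The rates come from "assuming the BF suspension rate at 6 months to be 60% in the control group versus 40% in the intervention group". The enrolment target and the expected loss stand at the end of the same section: "Compensating for an estimated loss rate of 20%, the estimated final total sample size would be 399 women".

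**The concern.** Coding missing outcomes in opposite directions by arm adds a difference that depends on the amount of loss rather than on the app. As an outer bound beside a main analysis, that is legitimate. Here it is the only content given to the ITT comparison, and section 4 asks that comparison to protect the randomization.

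The other analysis named is per-protocol. Section 2.2 excludes women who do not answer after three attempts, and control women who used the app on their own initiative. Both exclusions arise after randomization, and the second affects one arm only. If the app works as planned, the reader could be left with a per-protocol result open to selection and an ITT result that mainly measures how many women were lost.

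**Working it through.** **Inputs.** Suspension 60% control and 40% app, 20% loss, 399 women (section 2.4); outcome direction (section 2.7); coding rule and chi-square test (section 2.8). Assumptions added here: the same loss L in each arm, loss unrelated to feeding, no lost woman had already reported stopping, and two-sided 0.05.

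**The plan's own sample size.** For 60% versus 40% at two-sided 0.05 and 85% power:

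n per arm = [1.960·√(2·0.5·0.5) + 1.036·√(0.6·0.4 + 0.4·0.6)]² / 0.20² = 110.7, so 111 per arm and 222 in total (242 with continuity correction).

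The stated 333 is not reproduced; it equals 3 × 111. The 399 matches 333 × 1.2 = 399.6 rounded down. That is a separate matter, because the expected percentages below do not depend on N. It does affect how the 20% is read: if 333 of 399 women complete, loss is 66/399 = 16.5%. Both readings are carried forward.

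**Expected ITT rates under the rule.**

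- Control = 0.60 × (1 − L), since lost controls add no suspensions.
- App = 0.40 × (1 − L) + L, since every lost app woman adds one.
- Difference = 0.20 × (1 − L) − L, which is zero at L = 0.20/1.20 = 16.7%.

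At L = 20%: control 0.80 × 0.60 = 48%; app 0.80 × 0.40 + 0.20 = 52%. With 199.5 per arm, z = −0.04 / √(0.5 × 0.5 × 2/199.5) = −0.80, p about 0.42.

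**Chance of a significant result** (199 and 200 women, pooled z-test, equivalent to the uncorrected chi-square; exact binomial sums):

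| Loss per arm | Control | App | Significant benefit | Significant harm |
|---|---|---|---|---|
| 0% | 60.0% | 40.0% | 98% | under 0.1% |
| 5% | 57.0% | 43.0% | 79% | under 0.1% |
| 10% | 54.0% | 46.0% | 35% | under 0.1% |
| 15% | 51.0% | 49.0% | 6% | 0.8% |
| 16.5% | 50.1% | 49.9% | 2.5% | 2.2% |
| 20% | 48.0% | 52.0% | 0.3% | 12% |

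**Where the effect goes.** Coding losses as suspended in both arms at 20% loss gives control 0.48 + 0.20 = 68% versus app 52%, still 16 points for the app, with about 91% power at 399 women. The opposite coding by arm removes the effect, not caution as such.

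**The missing mirror image.** Reversing the rule at 20% loss gives control 0.48 + 0.20 = 68% and app 0.80 × 0.40 = 32%. The full range of the difference is therefore from 4 points against the app to 36 points for it. The plan computes only the first end.

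**Relaxing the assumption about earlier reports.** Take the extreme in which every lost control woman who would stop had already reported it and is counted as suspended. At 20% loss, control becomes 0.48 + 0.20 × 0.60 = 60%, and app stays at 52% because all lost app women are coded as suspended anyway. Then z = 0.08 / √(0.56 × 0.44 × 2/199.5) = 1.61, p about 0.11, and the chance of a significant benefit is about 37%. Most of the planned 20 points is still lost.

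**The case against.** The strongest reply is that section 2.8 itself labels the rule an assessment of sensitivity, and a worst-case bound is an accepted sensitivity analysis. The label does stand, and the rule is acceptable in that role. It does not settle the matter, because the text specifies no main ITT analysis for the bound to accompany. Nor can the point be set aside as detail left to an analysis plan: the article states a definite rule and test, and the objection is to that rule as the ITT comparison.

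It can also be said that the rule works against the app, is unlikely to produce a false claim of benefit, and is paired with a comparison of dropouts and completers. That is fair, but a result whose sign turns on the loss rate says little about the app, and describing dropouts does not estimate the effect.

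Several stronger readings are tempting and are not supported:

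- That the ITT analysis would show harm. At 16.5% loss the expected result is null, and at 20% a significant harm has only about a 12% chance.
- That section 2.4 promises 85% power for this comparison. It sizes the trial and then adds women for losses, which points to power among women with outcomes.
- That the efficacy conclusion must rest on the per-protocol set. Section 2.8.1 names no analysis set, so the text does not say so.
- That the rule overrides earlier reports of stopping. Section 2.5.1 collects feeding status after birth, at 15 days, 6 weeks and 3 months, and nothing says such reports are discarded.

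**Conclusion.** The point holds in this limited form. The only description of the ITT comparison is a one-directional bound, which cannot serve as the ITT estimate and gives no range without its mirror image. Under the plan's own 60% versus 40%, the expected result is about 50% versus 50% at 16.5% loss and 48% versus 52% at 20%. The planned benefit is erased or slightly reversed, usually without significance, and the chance of a significant benefit is about 0.3% to 2.5%.

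These figures assume equal loss in both arms, unrelated to outcome, with no earlier report of stopping, and a 0.05 threshold. The stricter 0.005 stated in section 2.8.2 is a separate inconsistency and would lower the chance of a significant benefit further. Earlier reports of stopping in the control arm would soften the figures but, even at the extreme shown, would not restore the planned effect.

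**What to change.** In section 2.8, state that the primary efficacy analysis in 2.8.1 compares all randomized women as allocated, using reported feeding status. Women who have already reported stopping count as suspended. Missing 6-month status is handled by a method that treats both arms alike. Multiple imputation within arm from earlier feeding reports and baseline factors is one sound option, not the only one.

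Keep the present rule, labelled explicitly as an outer-bound sensitivity analysis only. Add its mirror image, or a tipping-point analysis showing how different the lost women would have to be for the conclusion to change.

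The cost is revised wording and some programming; the feeding reports are already collected, so no new data or women are needed. The downside, if imputation is chosen, is that the main result rests on a missing-at-random assumption, which the retained bounds test.

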### 2.2. Recruitment

The study will be conducted in three public hospitals in eastern Spain (Hospital Lluis Alcanyis, Hospital General de Castellón, and Hospital Universitario de la Ribera), and in one hospital in the western part of the country (Hospital San Pedro de Alcántara de Cáceres). The four hospitals serve a total population of 500,000 inhabitants, with an average of 5000 births a year. The women will be included during the third trimester of pregnancy in the different primary care midwife consulting rooms of each of the participating centers.

The study exclusion criteria are: females under 16 years of age; women with cognitive impairments, language barriers, or illiteracy (not able to read Spanish); non-availability of a mobile device with internet connection; newborn infants with congenital malformations; twin or multiple pregnancies; and admission to the Neonatal Intensive Care Unit (NICU), prenatal death or stillbirth, or postpartum complications requiring admission of the mother to the intensive care unit (ICU). Women failing to respond to the automated messages from the platform after three attempts will also be excluded, in the same way as those women in the control group who have used the LactApp^®^ application on their own initiative. Figure 1 shows the monitoring to be carried out during the study.

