#### 2.8.2. Secondary Outcome

The level of HL (adequate vs. inadequate) with the HLS-EU-Q16 screening tool and the characteristics of the women who gave up BF at 6 months (yes/no) will be assessed via two-input tables with application of the chi-square test (χ^2^) for qualitative variables. Multivariate logistic models will be used in order to analyze the magnitude of the association with BF at 6 months. The adjusted odds ratio (OR) and 95% confidence interval (95%CI) will be calculated, and *p*-values will be presented.

Data analysis will be performed using SPSS v.26.0 for Windows (IBM Corp. 2018, Armonk, NY, USA) and R (R project 2019, version 4.0.2). The level of statistical significance defined was *p* < 0.005.

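### The only intention-to-treat rule given is a worst/best-case bound, which cannot show the planned benefit at the planned 20% loss and so cannot control loss-related bias

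*Protocol article*

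**What the plan says.** Section 2.8 names two analyses, PP and ITT. For the ITT analysis it says that sensitivity to losses will be assessed, with the "intervention group being assigned the worst result possible (suspension of BF at 6 months) and the control group being assigned the best result possible". The arms are then compared in all randomized women by chi-square. The article gives no other ITT handling of missing outcomes.

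Section 2.8.1 describes the primary comparison (chi-square and logistic regression) without naming a population.

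Section 4 gives the ITT analysis a specific job. "In order to control for such selection bias and break of randomization", it says, the dropouts will be described and an ITT analysis performed.

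The planning figures are in section 2.4. The suspension rates are set by "assuming the BF suspension rate at 6 months to be 60% in the control group versus 40% in the intervention group". Alpha there is 0.05 and power 85%. The total of 399 women is then reached by "Compensating for an estimated loss rate of 20" per cent.

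Section 2.2 adds exclusions that can arise only after allocation. "Women failing to respond to the automated messages from the platform after three attempts will also be excluded", and so will control women who used the app on their own initiative.

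**The concern.** Counting every lost app woman as a failure and every lost control as a success gives the outer limit of what the missing data could have done. It is useful as a bound. It is not an estimate of the effect among women as randomized, and it does not correct selection bias. It replaces a bias of unknown size with a large known one against the app.

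The article nevertheless makes this its ITT analysis and relies on it as the protection against loss. Outcomes come from e-mailed questionnaires and section 4 itself expects response to be a weakness, so the rule will apply to many women. Two errors are then possible: a real benefit cannot appear, and an app with no effect looks harmful.

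**Working it through.** **Plan's own figure.** For 0.60 against 0.40, two-sided alpha 0.05 (sidedness is not stated) and 85% power, the usual formula gives (1.96 × √(2 × 0.5 × 0.5) + 1.036 × √(0.24 + 0.24))² / 0.20² = 110.7, so 111 per arm and 222 in total. The plan says "a balanced design would require 333 women in total", so its figure is not reproduced. The 399 is 333 × 1.2 = 399.6, rounded down. Neither point affects what follows: the imputed rates depend only on the planned rates and the loss, and the probabilities use the 399 women actually planned.

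**Inputs.** Suspension 60% (control) and 40% (app), loss 20%, 399 women or 199.5 per arm (section 2.4). Alpha is 0.05 in section 2.4, but section 2.8.2 says "The level of statistical significance defined was *p* < 0.005", so both are shown. My assumptions: equal loss d in both arms, unknown 6-month status for every lost woman, and the planned rates holding among women with known status.

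**Imputed rates.**
- Control: 0.60(1 − d)
- App: 0.40(1 − d) + d
- Control minus app: 0.20(1 − d) − d, which is zero at d = 0.20/1.20 = 16.7%

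At d = 0.20, control is 0.60 × 0.80 = 48% and app is 0.40 × 0.80 + 0.20 = 52%.

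**Expected p at 20% loss.** The pooled standard error is √(2 × 0.5 × 0.5 / 199.5) = 0.0501. Then z = 0.04/0.0501 = 0.80 and p is about 0.42.

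**Chance of a significant result favouring the app.** This is Φ((difference − z_α × 0.0501)/s). Here s is the sampling standard error, with the number lost taken as fixed or as random. At 20% loss, s = √(2 × 0.24 × 159.6)/199.5 = 0.0439 (fixed) or 0.0500 (random). At alpha 0.05 this gives Φ(−3.15) = 0.1% or Φ(−2.76) = 0.3%.

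| Loss per arm | Control | App | Chance of significant benefit, alpha 0.05 | alpha 0.005 |
|---|---|---|---|---|
| 5% | 57.0% | 43.0% | 80–81% | about 50% |
| 10% | 54.0% | 46.0% | 35–36% | 10–11% |
| 15% | 51.0% | 49.0% | 4–6% | under 1% |
| 16.5% (399 to 333) | 50.1% | 49.9% | 2–3% | under 0.5% |
| 20% | 48.0% | 52.0% | 0.1–0.3% | under 0.1% |

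For comparison, the 319 women with known status at 20% loss (399 × 0.8), compared without imputation, give about 95% power at alpha 0.05 and 78% at 0.005. The information is there; the rule hides it.

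**No true effect (60% in both arms), 20% loss.** Control is 0.60 × 0.80 = 48%; app is 0.60 × 0.80 + 0.20 = 68%. The pooled standard error is √(2 × 0.58 × 0.42 / 199.5) = 0.0494. The chance of significant harm is Φ((0.20 − 1.96 × 0.0494)/s). With s = 0.0484 (random loss) it is 98%, and with s = 0.0439 (fixed) 99%. At alpha 0.005 it is 90% and 92%. At 10% loss the table is 64% against 54%, with significant harm in about 53% of trials at alpha 0.05.

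**The other named analysis.** A woman reaches the platform through the QR card in her allocation envelope (sections 2.3 and 2.5.1), so failing to answer it comes after randomization. Control use of the app is picked up in the follow-up surveys (section 4), also after randomization, and that exclusion applies to one arm only. A PP comparison after these exclusions has the selection problem that the ITT analysis was meant to answer.

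**The case against.** The strongest reply is that section 2.8 uses the word sensitivity, and worst/best case is a recognised stress test. That is fair, and the scenario deserves to be kept. But the text describes no base-case ITT analysis for it to test, and section 4 treats the ITT analysis as the control for bias.

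Other qualifications stand and limit the claim:

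- A reader might infer that PP is left as the only usable analysis. The article does not say so. Section 2.8.1 names no population, and an observed-case comparison by allocated arm would fit its wording.
- A reader might infer that the ITT result would point to significant harm under the planned effect. At 20% loss the reversal is 4 points, with significant harm expected in only about 9–12% of trials at alpha 0.05. If loss means 399 down to 333, the effect is cancelled, not reversed.
- A reader might see a contradiction between excluding non-responders (section 2.2) and analysing all randomized women (section 2.8). The two can be reconciled if non-responders leave the PP set and are the losses imputed in the ITT set.
- Some lost women will already have reported suspension, since feeding is asked about at earlier contacts. If that information is used, fewer than 20% need imputing and the distortion shrinks. The rule as written does not say that it is used.
- How PP and ITT are ranked may be left to an analysis plan not shown, so its absence is not the point here. The point is a missing-data rule that the article does state.

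**Conclusion.** The concern holds in this form: the one ITT handling of losses that the article describes is an extreme bound, and it cannot control selection bias as section 4 requires. At the planned rates and 20% loss it turns a 20-point benefit into a non-significant 4-point reversal, with under a 0.5% chance of showing the benefit. With no true effect it shows significant harm in about 98% of trials at alpha 0.05, and 90–92% at 0.005.

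These sizes rest on equal loss by arm, unknown status for every lost woman and 399 randomized. Lower loss softens them: at 5% loss, power is still about 80% at alpha 0.05. Because the rule bears on the primary conclusion and is stated rather than left open, it should be changed before the analysis.

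**What to change.** Reword section 2.8 as follows.

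1. The main analysis includes all randomized women in their allocated arm, including platform non-responders and control women who used the app.
2. A woman who has already reported total suspension counts as suspended, not missing. This convention treats total suspension as final and should be stated.
3. Remaining missing 6-month status is handled by a plausible method. Multiple imputation within arm, from baseline covariates and feeding status at birth, 15 days, 6 weeks and 3 months, is one suitable choice.
4. The worst/best case is kept as a labelled extreme sensitivity bound, not as the ITT result.
5. PP is supportive.

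The cost is a change of wording and a little more programming, with no new data collection. The downside is a missing-at-random assumption, which the retained sensitivity analysis tests.
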